## Abstract

**Background/Objectives**: Most survivors of out-of-hospital cardiac arrest (OHCA) may suffer from cognitive, mental difficulties, and fatigue, which negatively impact their quality of life, despite a good physical recovery. However, no definitive data are available on this topic, so this study aims to assess the feasibility and acceptability of a centralized, sub-regional screening system for OHCA survivors in Italy and the prevalence of these disorders. **Methods**: OHCA survivors discharged with good neurological outcomes (Cerebral Performance Category (CPC) ≤ 2 and modified Ranking Scale (mRS) ≤ 3) from hospitals in the “Lombardia CARe” registry will be evaluated by a clinical psychologist using the Montreal Cognitive Assessment (MoCA), Hospital Anxiety and Depression Scale (HADS), EQ-5D-5L for quality of life, and the Impact of Event Scale-Revised (IES-R) at pre-discharge or within 15 days and then at 1, 3, 6, and 12 months. Patients with clinical issues will be referred for psychological support or to a community rehabilitation program. Feasibility will be defined as a recruitment rate ≥ 80% and acceptability as a retention rate ≥ 50% over 12 months. **Results**: Based on historical data from the Lombardia CARe, an estimated 350 eligible survivors are expected, which will allow estimation of a prevalence ranging between 20% and 30% with 5% precision and 95% confidence. **Conclusions**: This study will be the first in Italy to evaluate the feasibility and acceptability of a centralized, sub-regional system for pre-/post-discharge evaluation of cognitive impairment, mental health, and quality of life in a large cohort of OHCA survivors, documenting the prevalence of these disorders.

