### 2.4. Statistical Methods

Baseline characteristics will be reported as means ± SD, or medians [IQR] for continuous variables, and as frequencies (%) for categorical variables. Prevalence of psychological distress, cognitive impairment, fatigue, symptoms of post-traumatic stress, and reduced quality of life will be estimated at all timepoints; exact 95% confidence intervals will be calculated. Reduced quality of life will be defined as an EQ-5D-5L VAS score at least 7 points lower than the age-matched Italian general population mean [26], based on established minimal clinically important differences identified in chronic disease populations [27,28].

Incidence rates (expressed per 100 person-years) for mood disorders, post-traumatic stress symptoms, reduced quality of life, and cognitive impairment will be calculated for participants free of the respective condition at baseline. Incident cases will be defined as follows: a HADS subscale score > 8 for mood disorders (either anxiety or depression subscale), IES-R ≥ 33 for post-traumatic stress symptoms, a MoCA score < 26 for cognitive impairment, and a decrease of ≥7 points from the age-matched normative mean on the EQ-5D-5L VAS for reduced quality of life. Baseline status will be determined using the initial T0 assessment; if T0 data are missing, the T1 (1-month) assessment will be used. Participants with missing data at both T0 and T1 for a given outcome will be excluded from the incidence rate calculation for that outcome. Incidence rates will be reported with exact 95% confidence intervals.

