### 3.2. Identification of Prevalence of Mood Disorders in OHCA Survivors

Based on Lombardia CARe figures, approximately 5200 OHCAs occur yearly in the regional area, and, in about 3500 of them, resuscitation is attempted. Of these, about 600 survive to hospital admission, and about 175 per year are discharged alive with CPC 1–2 or mRS ≤ 3. Therefore, over 24 months, about 350 eligible survivors are expected. Assuming 80% of them consent to be included in this study (about 280), this cohort will be sufficient to identify the presence of symptoms of at least mild anxiety or depression in 25% of cardiac arrest survivors at 6 months from the event, with 5% precision and 95% confidence (Appendix A, Table A2). Although the prevalence of mood disorders after OHCA has been investigated by several studies, REVIVE will be the first one to do so at the sub-regional level in Italy.

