**Intervista clinica semi-strutturata (original italian version)**
**Cognizione e funzioni cognitive:** *“Ha notato cambiamenti nella sua memoria, nella capacità di concentrarsi o nel trovare le parole giuste dopo la dimissione, e in che modo questi cambiamenti influenzano le sue attività quotidiane?”* 2. **Cognizione e funzioni cognitive:** *“Ha notato cambiamenti nella sua memoria, nella capacità di concentrarsi o nel trovare le parole giuste dopo la dimissione, e in che modo questi cambiamenti influenzano le sue attività quotidiane?”* 3. **Benessere emotivo e umore:** *“Nelle ultime settimane, ha provato sentimenti di ansia, umore depresso o ricordi indesiderati legati all’arresto cardiaco? In che modo questi sentimenti hanno influito su di lei o sui suoi familiari?”* 4. **Affaticamento e recupero fisico:** *“Prova stanchezza persistente, difficoltà di mobilità o limitazioni fisiche che rendono le attività di tutti i giorni più impegnative rispetto a prima dell’arresto cardiaco?”* 5. **Vita quotidiana, lavoro e indipendenza:** *“Ha riscontrato difficoltà nel riprendere le attività quotidiane importanti, come guidare, gestire i lavori domestici o tornare al lavoro? Ritiene di avere il supporto necessario per affrontare queste sfide?”* 6. **Informazioni necessarie e reti di supporto:** *“Lei e i suoi familiari sentite di avere le informazioni e il sostegno necessari—ad esempio, comprendete la funzione dei farmaci, sapete cosa aspettavi nei prossimi mesi, e siete in grado di accedere a supporto emotive/di mutuo aiuto—per gestire al meglio questa fase del recupero?”*

**Table A2 jcm-14-03631-t0A2:** Precision of the proportion estimate according to the number of patients enrolled and the proportion found.

Expected Proportion	Absolute Precision with 95% Confidence									
	0.01	0.02	0.03	0.04	0.05	0.06	0.07	0.08	0.09	0.10
**0.01**	381	96	43	24	16	11	8	6	5	4
**0.11**	3761	941	418	236	151	105	77	59	47	38
**0.21**	6373	1594	709	399	255	178	131	100	79	64
**0.31**	8217	2055	913	514	329	229	168	129	102	83
**0.41**	9293	2324	1033	581	372	259	190	146	115	93
**0.51**	9600	2400	1067	600	384	267	196	150	119	96
**0.61**	9139	2285	1016	572	366	254	187	143	113	92
**0.71**	7910	1978	879	495	317	220	162	124	98	80
**0.81**	5913	1479	657	370	237	165	121	93	73	60
**0.91**	3147	787	350	197	126	88	65	50	39	32

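### The Abstract's 5% precision for a prevalence of 20–30% rests on 350 eligible survivors; with the roughly 280 expected to consent it fails towards 30%

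*Protocol article*

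**What the plan says.** The Abstract (Results) gives the precision as follows: "350 eligible survivors are expected, which will allow estimation of a prevalence ranging between 20% and 30% with 5% precision", at a confidence level of 95%. It does not mention that only some eligible survivors will enrol.

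Section 3.2 starts from the same count, "Therefore, over 24 months, about 350 eligible survivors are expected", and then takes one more step: "Assuming 80% of them consent to be included in this study (about 280), this cohort will be sufficient". The aim it names is narrower than the Abstract's: "symptoms of at least mild anxiety or depression in 25% of cardiac arrest survivors at 6 months from the event, with 5% precision and 95%" (the last figure is the level of the interval). It refers to Appendix A, Table A2, whose title is "Precision of the proportion estimate according to the number of patients enrolled and the proportion found".

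For reporting, section 2.4 says of the prevalence estimates that "exact 95% confidence intervals will be calculated".

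**The concern.** The same 5% precision is stated twice, for different numbers of patients and different prevalences: 350 eligible for 20–30% in the Abstract, and about 280 enrolled for 25% in section 3.2. Only enrolled patients contribute to a prevalence estimate, so the Abstract uses a number that the body of the article and its own table do not use. The choice decides whether the claim holds, because the required number rises with prevalence between 20% and 30%.

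At stake is the stated precision of the prevalence aim, in the part of the article most often read. A study that exactly met its own 80% recruitment threshold (section 2.2) would not deliver the Abstract's figure at 30%. That end of the range is a realistic result: the Introduction cites emotional problems in around 15–30% of survivors at 6 months, and a pilot in which more than one-third had at least moderate depression.

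**Working it through.** **Inputs.** Eligible: 175 per year × 2 years = 350 (section 3.2). Consent: 80%, so 350 × 0.80 = 280 (section 3.2). Prevalence: 20–30% (Abstract) and 25% (section 3.2). Target half-width: d = 0.05 with 95% confidence, z = 1.96.

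**Reproducing the plan's table.** The normal-approximation formula n = z² p(1−p)/d² gives all 100 cells of Table A2 to within one patient. In the 0.05 column:
- p = 0.21: 3.8415 × 0.21 × 0.79 / 0.0025 = 254.9; the table has 255.
- p = 0.31: 3.8415 × 0.31 × 0.69 / 0.0025 = 328.7; the table has 329.

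**Number needed for 5 points at the prevalences claimed.** The table has no rows for these values, so the same formula is applied:
- 20%: 245.9, so 246
- 25%: 288.1, so 289
- 30%: 322.7, so 323

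**Half-widths.** With h = 1.96 × √(p(1−p)/n), in percentage points:

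| Prevalence | n = 350 | n = 280 |
|---|---|---|
| 20% | 4.19 | 4.69 |
| 25% | 4.54 | 5.07 |
| 30% | 4.80 | 5.37 |

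For example, at 30% with 280: 1.96 × √(0.21/280) = 1.96 × 0.02739 = 0.0537.

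The Abstract's range holds throughout at 350. At 280 the half-width is 5.00 points or less up to a prevalence of 24.0%, is 5 points to rounding at 25%, and is clearly above 5 at 30%.

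**Size of the gap at 30%.** 323 − 280 = 43 patients, or 43/323 = 13%. To enrol 323 would take 323/350 = 92% consent, or 323/0.80 = about 404 eligible survivors at the assumed 80%.

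**With the exact intervals that will be reported.** Clopper–Pearson half-widths (half the interval length) at 280 are 4.85, 5.23 and 5.52 points at 20%, 25% and 30%. At 350 they are 4.32, 4.67 and 4.93.

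**Attrition, as an illustration only.** The article gives no expected 6-month retention. If the 50% threshold that section 2.2 sets for 12 months is borrowed as a low case, 140 patients would be assessed, with normal-approximation half-widths of about 7.2 points at 25% and 7.6 at 30%. With all 280 assessed they are 5.07 and 5.37.

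**The case against.** The Abstract's arithmetic is correct for the number it names: 350 does give 5 points or better from 20% to 30%, even with exact intervals. The 80% consent assumption is disclosed in section 3.2, and the 0.31 row of Table A2 openly shows 329. At 30% the excess is 0.37 points, and no test, decision rule or feasibility threshold depends on it. All this is true. It makes the point an inconsistency of modest size, but the Abstract's sentence still promises a precision that the expected cohort does not give near 30%.

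Two stronger readings are tempting, and neither is supported.

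- A reader might infer that section 3.2 is also wrong, because 280 is below the 289 needed at 25%. But 5.07 points is 5% at the precision the article uses. A gap of 9 patients, about 3%, lies within the rounding of inputs that are all given as approximate. Section 3.2 uses the right number of patients, and its statement stands if all 280 are assessed.
- A reader might infer a larger shortfall from the exact method, since an average exact half-width of 5 points needs 306 patients at 25% and 341 at 30%. Section 2.4 sets exact intervals for reporting, not for sizing. Planning with the normal approximation and reporting exact intervals is common practice, and here the difference is about 0.15 points. It supports the point but does not carry it.

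**Conclusion.** The concern holds for the Abstract. Its 5% precision over 20–30% would require essentially all of the 350 eligible survivors to be enrolled and assessed: at 30%, 323 of them. With about 280 enrolled, the half-widths are about 4.7, 5.1 and 5.4 points at 20%, 25% and 30%, so the claim is met at 20%, met to rounding at 25%, and missed towards 30%.

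This rests on the article's own figures of 350 eligible and 80% consent, on the formula that reproduces Table A2, and on every enrolled patient being assessed. The last assumption is a best case, because section 3.2 places its estimate at 6 months and neither statement allows for loss to follow-up. The result does not make the sample size inadequate for a descriptive aim. It means that the stated precision should be corrected.

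**What to change.** In the Abstract, replace the 350 eligible with about 280 enrolled as the basis for precision. Then do one of the following:
- give 95% half-widths of about 4.7, 5.1 and 5.4 points at 20%, 25% and 30% (about 4.9, 5.2 and 5.5 with exact intervals); or
- limit the 5% claim to a prevalence of up to about 25%.

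In both the Abstract and section 3.2, state that the figures assume all enrolled patients are assessed at the time point named, which is 6 months in section 3.2, and that intervals will be wider with attrition. Describing them as precision at enrolment would not suit the 6-month aim.

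The cost is a few sentences. No extra patients and no design change are needed; the stated precision becomes slightly less favourable.

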## 1. Introduction

Out-of-hospital cardiac arrest (OHCA) is a leading cause of mortality worldwide, with overall survival rates estimated at 5–10% [1,2]. In Italy, about 60,000 OHCAs occur each year, with an incidence of about 1 case per 1000 inhabitants [3]. Among those who do survive, many achieve a good physical recovery yet may suffer from pronounced emotional or cognitive sequelae (e.g., rates of emotional problems and cognitive impairment at 6 months have been estimated at around 15–30% and 40–50%, respectively), along with fatigue [4,5,6]. These challenges can hinder a return to everyday life for both patients and relatives [7,8,9].

Guidelines from the European Resuscitation Council on the treatment of OHCA emphasize the importance of a systematic follow-up to screen for cognitive and emotional problems—for example, development of anxiety and depression or post-traumatic stress disorder symptoms—and to provide appropriate psychological support for patients and their families [6]. The importance of identifying (and meeting) the care and rehabilitation needs of survivors and their family members has also been recently highlighted by the Resuscitation Council UK [10] and translated for adoption by Fondazione IRC—the Italian non-profit organization dedicated to advancing the science and practice of resuscitation [11]. Some examples of post-discharge follow-up systems have been reported [12,13] alongside a framework for a multidisciplinary, guideline-based approach to improve the cardiac arrest pathway [14]. Guidelines and consensus statements also encourage the creation of multidisciplinary, holistic pathways of assessments and care [15,16,17]. Despite that, few structured programs exist globally, and few are currently in place in Italy. It is currently unclear which framework is best suited to deliver a comprehensive follow-up service that caters to the psychological/cognitive and physical needs of these patients; in addition, each healthcare system has unique implementation challenges. That notwithstanding, resource availability (i.e., personnel able to deliver the service) and access to appropriate training (i.e., how to deliver the service) are likely to be key issues.

During 2017–2018, the Cardiology Division of the Fondazione IRCCS Policlinico San Matteo, which is the coordinating centre of the Lombardia Cardiac Arrest Registry (LombardiaCARe), in collaboration with a non-profit organization (Pavia nel Cuore ODV) and the Psychiatry Unit of the University of Pavia, promoted a pilot study on the assessment of the psychological and emotional state of out-of-hospital cardiac arrest survivors in the Province of Pavia. This project showed that, in line with international data, more than one-third of patients discharged with a good neurological outcome (mRS ≤ 3) showed symptoms of at least moderate depression [18]. The incidence of depression was also higher in younger patients (<50 years old), in line with other observational studies [19,20,21], with mental health being particularly affected. The health-economic implications of this long-term burden are likely significant.

Building on those pilot data, this study aims to (a) investigate the feasibility and acceptability of a centralized, sub-regional assessment and follow-up system; and (b) to investigate the prevalence of psychological distress, cognitive impairment, and fatigue, as well as the degree of health-related quality of life in a large, multicentre cohort of OHCA survivors.

## 2. Materials and Methods

### 2.1. Study Design

This is a prospective, multicenter observational protocol, spanning 24 months, across 22 hospitals affiliated with the Lombardy Cardiac Arrest Registry (“Lombardia CARe”—a full list of the hospitals is provided in Table 1). This network covers a population of approximately 4.3 million people and includes densely populated urban areas and sparsely populated rural and mountainous locations.

In the REVIVE project, each of the 22 hospitals will have a named contact person (usually a senior cardiologist) who will enroll eligible survivors and inform the study team of the clinical status and readiness to be assessed before hospital discharge. Based on registry data from 2022, >90% of patients with a good neurological outcome (CPC 1–2; mRS ≤ 3) were discharged from 11 hospitals affiliated to this network, therefore these sites have been highlighted in Table 1 as ‘Main Recruiters’ and a picture describing their approximate location in the Lombardy region is provided (Figure 1).

The REVIVE project plans to enroll consecutive OHCA survivors meeting eligibility criteria and to follow them up for 12 months post-discharge. Survivors will be assessed at five different timepoints: **T0**—before discharge (or within 15 days post-discharge); **T1**: 1 month post-discharge; **T2**: 3 months post-discharge; **T3**: 6 months post-discharge; **T4**: 12 months post-discharge.

At each time point, the same battery of questionnaires will be administered **in-person or over the telephone/via telemedicine**, based on patient preference and feasibility.

Should a significant need be identified, the study team will, in the first instance, consider whether psychological therapy/cognitive rehabilitation can be provided in-house; however, it is expected that most patients will be referred to community-based rehabilitation programmes or other specialists where required.

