#### 2.1.3. Enrolment and Assessments

The Lombardia CARe Registry records all admissions of patients who have suffered an out-of-hospital cardiac arrest across seven provinces in the Lombardy region, updated to the previous 24 h. This registry is monitored daily by the team involved in this study; for patients admitted to the IRCCS Policlinico San Matteo Hospital in Pavia, their clinical history (including survival and neurological status) is monitored via the hospital internal electronic system and, if eligible, they are approached to provide consent for participation to this study close to their discharge day, usually in the cardiology ward. For those patients admitted to one of the ten other main recruiting hospitals (Figure 1), the local investigator will approach them for screening and enrollment. They will also inform the study team about their clinical status and readiness for assessment before hospital discharge. To minimize the risk of patients being missed, an email will be sent to all the investigators of the main recruiting hospitals every Monday and every Friday. The secondary recruiting centres do not have an allocated local investigator, so they will be contacted as and when required.

Most eligible patients are supposed to be approached before hospital discharge; if not, the study management team will contact them within 15 days post-discharge. Following informed consent, baseline assessment will be conducted by a clinical psychologist, either in-person (for patient admitted to Fondazione IRCSS San Matteo hospital, Pavia) or remotely (via telephone call or telemedicine, for all other patients), using measures of cognitive ability (Montreal Cognitive Assessment [22]), anxiety and depression [23], health-related quality of life [24], and symptoms of post-traumatic stress disorder [25]. Parallel versions of the cognitive assessment will be administered to reduce practice effects. A list of all measures and their purpose is described in Table 2.

In addition to quantitative instruments, starting from the first follow-up after hospital discharge (that is, the 1-month follow-up), patients will also undergo a brief semi-structured, qualitative interview focused on their own subjective experience of returning to day-to-day life, fatigue, cognitive problems, mood difficulties, and their ability to access appropriate information/support about their condition (Appendix A; Table A1).

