Longitudinal changes in HADS, MoCA, EQ-5D-5L, and IES-R from T0 to T4, as well as differences in the retention rate between patients seen remotely or face-to-face, will be analyzed using mixed-effects models (linear or logistic) incorporating time and potential covariates (e.g., age, sex, comorbidities). Models will initially include random intercepts and slopes at participant and hospital levels. Different residual covariance structures (e.g., first-order autoregressive [AR(1)]) will also be explored. Model selection will be guided by the Akaike Information Criterion (AIC) and Bayesian Information Criterion (BIC); simpler random intercept-only models will be adopted if convergence issues arise. Missing data will be handled using Multiple Imputation by Chained Equations (MICE), assuming a Missing At Random (MAR) mechanism. Twenty imputed datasets will be generated, incorporating all key predictors and outcomes, as well as hospital ID. Participants who completely withdraw from this study will be treated as censored at their last observation without further imputation. Sensitivity analyses comparing complete-case and imputed datasets will be conducted to assess the robustness of the findings. A *p*-value < 0.05 (two-sided) will denote statistical significance.

Qualitative data will be derived from detailed notes taken during semi-structured interviews; the analysis will employ a framework approach, well-suited for applied qualitative research with pre-defined areas of inquiry [29]. The analytic process will involve familiarization with the notes, followed by the development of a thematic framework based on the predetermined domains. Data will then be indexed using both deductive codes—stemming from the interview guide—and emergent codes that may arise from the content of the notes. A matrix will be constructed to chart responses across cases, enabling systematic cross-case comparisons.

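### T0 may fall before discharge or up to 15 days after, yet section 2.4 uses it as one timepoint, so T0 prevalence, condition-free status at baseline and early change depend partly on when T0 was done

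*Protocol article*

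**What the plan says.** Section 2.1 (Study Design) lists five assessments. T0 is "before discharge (or within 15 days post-discharge", with no earliest day given. T1 is "1 month post-discharge", and T2 to T4 are likewise counted from discharge.

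Section 2.1.3 (Enrolment and Assessments) explains how a late T0 arises. Most eligible patients are meant to be approached in hospital; "if not, the study management team will contact them within 15 days post-discharge".

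Section 2.4 (Statistical Methods) uses T0 in three ways:

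- Prevalence is estimated once per timepoint, T0 included.
- For incidence, "Baseline status will be determined using the initial T0 assessment; if T0 data are missing, the T1 (1-month) assessment will be used". Patients who already have the condition at that assessment are not at risk.
- "Longitudinal changes in HADS, MoCA, EQ-5D-5L, and IES-R from T0 to T4" are analysed with mixed-effects models that include time and covariates. Age, sex and comorbidities are given as examples.

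Nowhere does the article separate a pre-discharge T0 from a post-discharge one. The only sensitivity analysis named compares complete-case with imputed data.

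**The concern.** T1 to T4 are anchored to discharge and T0 is not. A T0 on the ward and a T0 two weeks after going home measure different things. The first precedes the return to daily life; the second already contains part of it and lies about halfway to T1. Mood, post-traumatic symptoms and self-rated health could plausibly move over that period.

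Three planned results depend on T0. T0 prevalence becomes a mixture of two settings. The set of patients counted as condition-free, and so the numerator and denominator of each incidence rate, depends on the T0 date. The change from T0 to T1 covers unequal intervals and, for late T0s, leaves out the move home.

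**Working it through.** **1. The plan's own figure.** Section 3.2 states that about 280 patients (80% of 350) estimate a prevalence of 25% at 6 months to within 5 points with 95% confidence. The formula is n = z² p(1 − p)/d² = 1.96² × 0.25 × 0.75/0.05² = 288.1. Conversely, the half-width at n = 280 is 1.96 × √(0.25 × 0.75/280) = 5.07 points, which is 5 after rounding. The figure concerns 6 months, so the T0 window does not enter it. It serves below only as a yardstick.

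**2. Interval from T0 to T1.** Input: the T0 window in section 2.1, with one month taken as 365.25/12 = 30.4 days. Gap = 30.4 − (day of T0 after discharge).

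| T0 day | Gap to T1 (days) | Relative to day 0 |
|---|---|---|
| −14 (assumed) | 44.4 | 1.46 |
| −7 (assumed) | 37.4 | 1.23 |
| 0 | 30.4 | 1.00 |
| 15 | 15.4 | 0.51 |

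The window after discharge alone gives a two-fold spread. The negative days are illustrations, because no earliest day is stated.

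**3. Baseline status.** This step needs no assumed rate. Take a patient whose HADS subscale score first exceeds 8 on day 10 after discharge and is still above 8 on day 15 and at T1.

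- With a ward T0, the patient is condition-free at baseline and becomes an incident case.
- With a T0 on day 15, the patient is a prevalent case and leaves both numerator and denominator.

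The reverse also occurs. A patient above the cut-off on the ward who has recovered by day 15 is excluded with a ward T0 and at risk with a late one. The direction of the net effect is therefore not fixed. The T1 fallback carries the same dependence out to one month.

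**4. Pooled T0 prevalence.** Shift = (share of late T0s) × (difference in prevalence between settings). Neither input is in the article. Assuming a difference of 5 to 10 points:

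- 10% late: 0.5 to 1.0 points
- 25% late: 1.25 to 2.5 points
- 50% late: 2.5 to 5.0 points

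The yardstick is the 5.07-point half-width for 280 patients at 25% prevalence.

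**5. Change from T0 to T1, if time is coded by nominal visit.** Assume linear change over the first month and all other T0s at day 0. Attenuation of the mean change = (share late) × (mean late day)/30.4. With a mean late day of 7.5 to 15:

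- 10% late: 2.5% to 4.9%
- 25% late: 6.2% to 12.3%
- 50% late: 12.3% to 24.6%

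If time is coded in actual days, this part disappears. The difference in setting remains, and so does the effect on steps 3 and 4.

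**6. Person-time.** From T0 to T4 is about 365 days from day 0 and 350 days from day 15, so at most about 4% is lost. Person-time is a minor matter; classification in step 3 is the main one.

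**The case against.** The strongest reply is that this is an ordinary, openly stated baseline window with late T0 as the exception. Section 2.1.3 expects most patients to be approached in hospital and describes daily registry monitoring and twice-weekly reminders. Section 2.1 attributes more than 90% of good-outcome discharges to 11 hospitals, so centres contacted only as needed would supply fewer than about 28 of 280 patients. The article does not say that model time is nominal, its covariates are only examples, and a condensed article may leave both to a fuller document. All of this stands. It limits the likely size and means the longitudinal model cannot be called wrong as written. It does not answer the baseline rule, which section 2.4 fixes explicitly on T0 status whenever T0 was done.

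Three stronger readings are tempting and not supported.

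- **That the early scores are off by an amount close to the plan's 7-point threshold on the EQ VAS.** An assumed linear recovery of 10 points over 30 days puts a day-15 T0 5.0 points (10 × 15/30) above one at discharge. That is the shift for one patient, on a recovery figure the article does not give. With late T0s averaging day 7.5, the pooled mean moves by 2.5 points × the late share: 0.25 points at 10% and about 0.6 at 25%. The 7 points are also measured from an age-matched norm, not between visits.
- **That the hub and the other hospitals must differ at T0.** This needs unequal late shares, which the article does not report. The planned comparisons by modality concern recruitment, attrition and retention, not T0 scores.
- **That the main aims are compromised.** The recruitment and retention criteria and the 6-month precision figure do not use T0 scores.

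**Conclusion.** The point holds within limits. T0 is a floating visit set against fixed later ones, and section 2.4 uses it as one timepoint for T0 prevalence and condition-free status. Incidence therefore depends in part on when T0 took place, and early change does too. Two facts rest on the article alone: the roughly two-fold spread in the interval to T1 (15.4 to 30.4 days, more for ward assessments), and the reclassification of the same patient.

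The size of any bias is unknown. The ranges for pooled prevalence and attenuation rest on assumed late shares and setting differences. With few late T0s, as the plan intends, they are small: at 10% late, 0.5 to 1.0 points on T0 prevalence and 2.5% to 4.9% on early change under nominal time. This is a modest weakness in secondary parts of the analysis, worth correcting because the correction is nearly free.

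**What to change.** In section 2.4:

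- **Longitudinal models.** State that time is the actual number of days from discharge at each assessment (zero or negative for ward assessments), and add an indicator for T0 done before versus after discharge.
- **Prevalence and incidence.** Report the distribution of T0 timing, including how many patients took baseline status from T1. Repeat the T0 prevalence and incidence analyses in patients with a pre-discharge T0, as a sensitivity analysis.

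A separate T0 prevalence for the late group should not be a main result. If 28 patients were late (10% of 280, assumed), its half-width at 25% prevalence would be 1.96 × √(0.25 × 0.75/28) = 16 points. Patients with a pre-discharge T0 may also differ from the rest in other ways, so a difference in the sensitivity analysis would not be due to timing alone.

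The cost is one model term and one sensitivity analysis. Assessment and discharge dates are already needed to schedule visits. No visit, recruitment or sample-size change follows.
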